5.3 Evaluation and Examination During Treatment

1. After completing each treatment cycle, patients were required to have a complete blood count examination every 3 days and coagulation function, liver, and kidney function examinations weekly. The main indicator values were documented during the process.
2. Physical examination, toxicity assessment, and pre-chemotherapy assessment (including complete blood count, biochemical routine, coagulation function, EBV-DNA, serum amylase, urine protein and urinalysis, stool routine + occult blood, serum β2-MG, thyroid function, six items of cardiac function, electrocardiogram, echocardiography, and for hepatitis B or C patients, HBV-DNA and HCV-RNA testing).
3. Chimerism Analysis: on the day 7 after UCB infusion, peripheral blood cells were collected from all patients and assessed for chimerism using standard cytogenetic and a semi-quantitative polymerase chain reaction based assay of short tandem repeats with the sensitivity of 1%.

5.4 Monitoring of Minimal Residual Disease (MRD)

- Leukemia-associated immunophenotyping (LAIP) was determined at diagnosis using different surface antigens.

- Monoclonal antibodies against 20 antigens were utilized: CD2, cyCD3, CD4, CD7, CD11b, CD13, CD14, CD15, CD19, CD33, CD34, CD38, CD45, CD56, CD64, cyCD79a, CD117, HLA-DR, MPO, and TdT.

- A cut-off value of 0.01% was set for defining MRD negativity.

5.5 Follow-up Evaluation

Schedules:

- Post-UCB treatment on days 14, 30, and 60.

- Before each chemotherapy session and before and after each maintenance treatment during the treatment period.

- After the end of treatment, follow-up assessments were performed monthly in the first year, and every three months thereafter.

Testing Items:

- Bone marrow aspiration smear, MRD, bone marrow chimerism detection.

- Chromosome testing was required after consolidation and maintenance therapy.

- If there was any disease recurrence detected by bone marrow cytology at any time during the treatment, the treatment will be deemed ineffective. Then the patient will be withdrawn from this study and enter the trials for relapsed and refractory AML treatment.

- If bone marrow chimerism > 30% at any time during treatment, donor engraftment will be considered, and the patient will be withdrawn from the clinical trial and receive anti-rejection treatment.

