**1. Background**

Acute myeloid leukemia (AML) is a clonal malignancy, characterized by aberrant differentiation of hematopoietic stem and progenitor cells. The global incidence of AML increased to 144,645 in 2021, with the age-standardized incidence rate of 1.73/100,000.^1^ Particularly, the incidence of AML increases with age. American and China had the highest incidence cases, with 21,533 and 17,835 AML cases in 2021, respectively.^1^ Moreover, American also showed the highest deaths while China had the highest disability-adjusted life years of AML.^1^

AML treatments consist of initial induction therapy and post-remission therapy. Despite a high initial complete remission (CR) rate after induction therapy,^2,3^ most patients die of relapsed AML. Relapse is the most frequent cause of treatment failure in AML.^4^ Moreover, older patients (age ≥ 60 years) with AML in CR have a much higher relapse rate of 80-90% compared to less than 50% in younger patients.^5,6^ Thus, appropriate post-remission therapy is critical once CR is achieved after induction therapy.

Common post-remission treatment strategies include additional cytotoxic chemotherapy (such as high or intermediate dose of cytarabine) or allogenic hematopoietic stem cell transplantation (allo-HSCT), with or without targeted therapy. Currently, allo-HSCT remains the potentially curative option in patients with AML. Most patients aged ≥ 60 years cannot proceed to allo-HSCT, due to multiple reasons including lack of donor, personal choice and biological factors. As previously reported, only 24% of older patients proceeded to allo-HSCT after intensive therapy.^7^ Meanwhile, targeted therapy may not be available due to lack of targets or lack of access for many patients. Consolidation with chemotherapy is thus administered for these patients. Unfortunately, high or intermediate dose of cytarabine consolidation did not produce prognosis benefits in elderly patients with AML.^8-10^ This leads to highly unsatisfactory outcomes in elderly AML patients. There remains an unmet medical need for these patients.

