2.2 Study Endpoints

2.2.1 Primary Endpoint

- Overall Survival (OS): defined as the time interval from the date of diagnosis to date of death from any cause, with censoring of patients known to be alive upon the last follow-up.

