3.2 Planned Sample Size

This study is a phase 2 clinical trial using a single-arm, single-stage design method to calculate the sample size. The primary endpoint is the 2-year OS of all enrolled patients. Based on prior knowledge, the 2-year OS with standard chemotherapy is about 50%. Assuming the 2-year OS expectation with UCB treatment is 67%, with P1 = 0.67 (superior) and P0 = 0.50 (inferior), α = 0.05, β = 0.20, and considering a 5% expected dropout rate, the study plans to enroll approximately 52 patients.

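### Section 5.5 withdraws on-treatment relapsers from the study without saying that survival follow-up continues, so the primary 2-year OS may be informatively censored and biased upward

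*Protocol*

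**What the plan says.** Section 5.5 of the protocol has two withdrawal rules.

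- **Relapse.** The trigger is "If there was any disease recurrence detected by bone marrow cytology at any time during the treatment". The consequence is: "Then the patient will be withdrawn from this study and enter the trials for relapsed and refractory AML treatment".
- **Chimerism.** When marrow chimerism exceeds 30% during treatment, "the patient will be withdrawn from the clinical trial and receive anti-rejection treatment".

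Both rules take the patient out of the study or trial, not only off study treatment. The same section sets the later schedule: "After the end of treatment, follow-up assessments were performed monthly in the first year, and every three months thereafter". It does not say whether this covers withdrawn patients.

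The primary endpoint in Section 2.2.1 runs from diagnosis to "date of death from any cause, with censoring of patients known to be alive upon the last follow-up". Section 3.2 fixes the measure: "The primary endpoint is the 2-year OS of all enrolled patients". Section 5.2 allows maintenance in 28-day cycles and states no number of cycles. Sections 7.3.2, 7.3.3 and 7.3.5 together require deaths, including deaths from progression, to be reported as SAEs up to 90 days after the last administration.

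**The concern.** OS in all enrolled patients can be measured only if deaths are known for all enrolled patients. If withdrawal at relapse also ends follow-up, the last follow-up is at about the time of relapse, and the OS definition then censors the patient there. Kaplan-Meier treats a censored patient as having the same outlook as those still under observation. Here those still under observation are mostly in remission, whereas the censored patient has just relapsed. Section 1 itself says that most patients die of relapsed AML. The censoring would be informative, and it would always push OS upward.

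This is a single-arm trial judged against a fixed 50%, so no control group shares the bias. An analysis plan cannot repair it either, because it cannot recover deaths that were never collected.

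**Working it through.** **1. The plan's own figure.** Section 3.2 gives P0 = 0.50, P1 = 0.67, α = 0.05, β = 0.20 and 5% dropout. With one-sided α and the variance under P1:

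n = (1.645 + 0.842)² × 0.67 × 0.33 / 0.17² = 47.3, so 48; 48 / 0.95 = 50.5, so 51.

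This is close to the stated 52, and the sample size is not in dispute. What matters here is that the planned effect is 17 points, and that the dropout allowance is 5%, about 3 of 52 patients. The Background reports that older patients in remission "have a much higher relapse rate of 80-90% compared to less than 50% in younger patients".

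**2. Model for the bias if follow-up stops at withdrawal.** The protocol does not give these inputs, so they are assumptions:

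- Hazards are constant and the clock starts in remission.
- The total hazard of leaving remission is λ. Relapse is the first event in a share p = 80-90%. This borrows the Background figure, which has no time horizon and is not itself a share of first events.
- Hazard of death after relapse is μ = ln 2 / m, with median m = 6 to 12 months.
- True 2-year OS is 50%.

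True survival is S(t) = exp(−λt) + [pλ/(μ − λ)] × [exp(−λt) − exp(−μt)], and λ is solved so that S(24) = 0.50.

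If relapsers are censored at relapse during a treatment period of D months, only patients in remission remain at risk up to D. The Kaplan-Meier estimate at 24 months then tends to

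KM = exp(−(1 − p)λD) × S(24 − D).

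Example with p = 0.85 and m = 9: μ = 0.0770 and λ = 0.0550. For D = 12, KM = 0.906 × 0.772 = 0.699. For D = 24, KM = exp(−0.15 × 0.0550 × 24) = 0.820.

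**3. Results** over p = 80, 85, 90% and m = 6, 9, 12 months. The last column counts every death in the 3 months after relapse, as a rough allowance for SAE reporting.

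| Treatment period | Censored at relapse | Deaths within 3 months of relapse counted |
|---|---|---|
| 2 months | 53-54% | 52-53% |
| 6 months | 58-61% | 56-58% |
| 12 months | 65-73% | 61-65% |
| 24 months | 73-90% | 64-70% |

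The SAE allowance is generous, because the 90 days run from the last administration and not from relapse.

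**4. Share of deaths lost.** A separate simulation assumed 2-year relapse of 40-70%, median survival after relapse of 4-9 months and 10% two-year death without relapse, with no SAE capture. It lost 11-17%, 30-43%, 54-70% and 74-91% of 2-year deaths for treatment of 2, 6, 12 and 24 months.

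**5. Chimerism rule.** The protocol gives no expected frequency for marrow chimerism above 30%, so its contribution cannot be calculated.

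**The case against.** The strongest reply is that the protocol never orders OS to be censored at relapse or withdrawal. The definition counts any death and censors only patients known to be alive. Section 9.2 keeps every enrolled and treated patient in the full analysis set, apart from serious eligibility violations. Withdrawal may only be meant to free the patient for another trial, since Section 5.6.2 bars other experimental drugs and chemotherapy during this one. Section 10.3 mentions keeping identity records for long-term follow-up. The 90-day SAE window governs safety reporting and does not limit how OS data are collected.

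Much of this stands. A reader might infer that most deaths would be censored and 2-year OS badly overstated. The documents do not support that as a stated consequence, for these reasons:

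- It needs the premise that withdrawal ends collection of vital status, which the protocol neither states nor excludes.
- The relapse rule covers relapse during treatment only. More than half of deaths are lost only if treatment lasts about 12 months or longer.
- The 73-90% range needs a treatment period that fills all 24 months.
- The 80-90% relapse rate carries no time horizon, and survival after relapse is assumed.

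The reply does not close the gap. The OS definition need not name withdrawal as a censoring reason: if follow-up ends there, that date is the last follow-up. Membership of an analysis set does not supply a death date, and retaining identity records is not a follow-up schedule.

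**Conclusion.** The point holds in conditional form. Read literally, Section 5.5 removes on-treatment relapsers, and patients above 30% chimerism, from the study. Nothing in the protocol keeps them in survival follow-up, which conflicts with a primary endpoint of 2-year OS in all enrolled patients. If follow-up stops, OS is overstated.

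Under the assumptions above, with a true 2-year OS of 50%, the overstatement runs from about 3 points for a 2-month treatment period to about 40 points at the extreme for 24 months. At 12 months it is 15-23 points without SAE capture and 11-15 with it, against a planned effect of 17. Because treatment duration is not stated, the protocol does not show where in this range the trial falls. If vital status was collected after withdrawal and OS was not censored there, this bias is zero.

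**What to change.** - In Section 5.5, state that withdrawal ends study treatment and protocol procedures only.
- State that every enrolled patient is followed for vital status to the data cut-off (31 March 2023 in Section 15), whatever the relapse status, chimerism or later therapy.
- Add to the OS definition that withdrawal is not a reason for censoring.
- For patients already withdrawn, obtain the date of death or the date last known alive.
- If deaths after withdrawal were collected all along, say so; that settles the point.

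The cost is a few sentences and a small vital-status sweep among 51 enrolled patients. The reported OS may fall. The clinical decision to stop study treatment is not questioned.

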5.6 Concomitant Medications and Management

5.6.1 Permitted Concomitant Treatments:

- Antiemetics may be used prior to the administration of chemotherapy drugs.

- Blood products (suspended red blood cells, single donor platelets, plasma, Fg, etc.) may be used as supportive therapy.

- During the treatment process, broad-spectrum antibiotics (antibacterial/antifungal), growth factors (G-CSF/GM-CSF, IL-11, and TPO, etc.), and hepatoprotective drugs may be used, according to the patient's condition.

5.6.2 Prohibited Treatments:

- During the trial, patients were prohibited from using other experimental drugs, radiotherapy, chemotherapy, and other treatments that may interfere with the study.

**6. Efficacy Evaluation**

6.1 Efficacy Indicators

- OS

- EFS

- Neutrophil and platelet recovery

6.2 Definitions of Efficacy Indicators

- OS: defined as the time interval from the date of diagnosis to the date of death from any cause, with censoring of patients known to be alive upon the last follow-up.

- EFS: determined as the time interval from the date of diagnosis to the date of occurrence of any following events, including relapse or death, whichever came first.

- Neutrophil and platelet recovery: the median times to recovery of neutrophils (≥ 0.5 × 10⁹/L) and platelets (≥ 20 × 10⁹/L and ≥ 50 × 10⁹/L).

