2.2.2 Secondary Endpoints

- Event-free Survival (EFS): defined as the time interval from the date of diagnosis to the date of occurrence of any following events, including relapse or death, whichever came first.

- Bone marrow measurable residual disease (MRD) by flow cytometry.

- The median times to recovery of neutrophils (≥ 0.5 × 10⁹/L) and platelets (≥ 20 × 10⁹/L and ≥ 50 × 10⁹/L) documented for each patient.

- Safety: including hematological and non-hematological adverse events (AEs) and the severity of AEs assessed following the National Cancer Institute Common Terminology Criteria for Adverse Events (NCI-CTCAE, v5.0).

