- Chemotherapy-Induced Thrombocytopenia (CIT): Refers to the inhibition of bone marrow, especially megakaryocytes, by chemotherapy drugs, causing peripheral blood platelet counts to drop below 100×10⁹/L.

a). Treatment of CIT: Platelet transfusion, administration of platelet growth factors such as recombinant human interleukin-11 (rhIL-11) or recombinant human thrombopoietin (TPO).

b). rhIL-11 Administration: rhIL-11 should be used when platelet counts are 25~75×10⁹/L. Recommended dose is 25~50 µg/kg, subcutaneously, once daily for at least 7-10 days. Discontinue when platelet count reaches 75×10⁹/L.

c). rhTPO Administration: If chemotherapy drugs are expected to cause thrombocytopenia and induce bleeding, requiring increased platelet counts, administer subcutaneously 6-24 hours after chemotherapy ends, at a dose of 300 U/kg daily for 7-10 days. Regularly monitor complete blood counts, usually every other day, and discontinue when platelet count reaches 75×10⁹/L.

3) Anemia

- Cancer-Related Anemia (CRA): Refers to anemia occurring during cancer progression and treatment. Laboratory tests are needed to determine the cause. Treatment principles are as follows:

a). Non-Chemotherapy-Related Anemia: Provide targeted treatment for different causes.

Nutritional anemia: Supplement with iron, folic acid, and vitamin B12; autoimmune anemia: Treat with corticosteroids (if not contraindicated); tumor-related inflammation or chemotherapy-induced bone marrow suppression: Evaluate the risk-benefit of treatment and decide whether to use blood transfusions or erythropoiesis-stimulating agents (EPO).

b). Red Blood Cell Transfusion: Quickly increases hemoglobin (HGB) and hematocrit (HCT). In China, blood transfusion is recommended when HGB < 6 g/dL. Consensus on transfusion in China: Severe or above anemia patients; moderate anemia with severe symptoms; EPO ineffective patients.

c). EPO: Takes weeks to stimulate HGB elevation but is effective in maintaining HGB at an appropriate target level. For leukemia chemotherapy-induced anemia, consider using EPO after evaluating the risk of thrombosis.

d). Parenteral Iron Supplements: Treat iron-deficiency anemia (transferrin saturation < 15%, serum ferritin < 30 ng/mL) with oral or intravenous iron supplements without simultaneous EPO. Low-molecular-weight dextran iron, ferric gluconate, or ferric sucrose are recommended due to fewer side effects.

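### Platelet recovery is defined by a count threshold alone while platelet transfusion is allowed, so the 20 × 10⁹/L recovery time can be biased short

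*Protocol*

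**What the plan says.** Section 6.1 lists neutrophil and platelet recovery as one of three efficacy indicators, next to OS and EFS. Section 6.2, which is the definitions section, gives the platelet rule as "platelets (≥ 20 × 10⁹/L and ≥ 50 × 10⁹/L". Section 2.2.2 repeats it among the secondary endpoints: "platelets (≥ 20 × 10⁹/L and ≥ 50 × 10⁹/L) documented for each patient". Neither place puts a condition on how the count was reached.

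Platelet support is allowed elsewhere in the protocol. Section 5.6.1 states: "Blood products (suspended red blood cells, single donor platelets, plasma, Fg, etc.) may be used as supportive therapy". It also allows "growth factors (G-CSF/GM-CSF, IL-11, and TPO, etc". For chemotherapy-induced thrombocytopenia, section 7.6.1 lists "Platelet transfusion, administration of platelet growth factors such as recombinant human interleukin-11 (rhIL-11) or recombinant human thrombopoietin (TPO". On rhIL-11 it adds: "rhIL-11 should be used when platelet counts are 25~75×10⁹/L".

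Section 5.3 sets the sampling after each cycle: "complete blood count examination every 3 days".

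**The concern.** Time to platelet recovery is meant to show when the patient's own marrow again maintains a platelet count. A transfusion raises the measured count for some days whatever the marrow is doing. If a threshold count is enough by itself, a sample taken shortly after a transfusion can be recorded as the recovery date.

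The lower threshold is the more exposed one. Transfusions are given at low counts, and a modest increment can carry a patient past 20 × 10⁹/L. Passing 50 × 10⁹/L needs a much larger rise.

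What is at stake is how a secondary efficacy endpoint is read. The trial has a single arm, so no concurrent control group shares the bias. Any comparison of the 20 × 10⁹/L median with outside experience would mix transfusion practice with haematological recovery.

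**Working it through.** **Figure to reproduce.** There is none. The protocol states no recovery median, transfusion frequency or transfusion trigger.

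**Step 1: direction.** On the scheduled sampling days, the measured count is the patient's own count plus surviving transfused platelets. Hence:

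- measured count ≥ own count on every day;
- first day with measured count ≥ threshold ≤ first day with own count ≥ threshold;
- first day with measured count ≥ threshold ≤ first such day that is also transfusion-free.

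This holds for each patient and therefore for the median. The written rule gives a time that is shorter or equal, whatever the transfusion practice.

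**Step 2: illustration of size.** Only the 3-day sampling comes from the protocol. Everything else is assumed:

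- own count at a nadir of 5 to 12 × 10⁹/L (uniform) until marrow recovery starts, at mean day 18 (SD 4);
- growth after that by a factor exp(0.22) per day;
- transfusion whenever the daily count is below a trigger of 10 or 20 × 10⁹/L;
- mean increment of 15, 30 or 45 × 10⁹/L;
- half-life of transfused platelets of 2 or 3 days;
- 4,000 simulated patients per scenario.

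The comparison rule is the first sampled count at or above the threshold with no transfusion in the previous 7 days. It did not also require consecutive counts.

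The unsupported benchmark follows from the model at the middle nadir of 8.5:

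- to 20: 18 + ln(20/8.5)/0.22 = 18 + 3.9 = day 21.9, first sampled on day 24;
- to 50: 18 + ln(50/8.5)/0.22 = 18 + 8.1 = day 26.1, first sampled on day 27.

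Median days in the 12 scenarios:

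| Trigger | Increment | Half-life (days) | ≥20 as written | ≥20, 7-day rule | Patients dated earlier at ≥20 | ≥50 as written | ≥50, 7-day rule |
|---|---|---|---|---|---|---|---|
| 10 | 15 | 2 | 21 | 24 | 39% | 27 | 27 |
| 10 | 15 | 3 | 18 | 24 | 47% | 27 | 27 |
| 10 | 30 | 2 | 12 | 24 | 65% | 27 | 27 |
| 10 | 30 | 3 | 9 | 24 | 69% | 27 | 27 |
| 10 | 45 | 2 | 9 | 24 | 71% | 27 | 27 |
| 10 | 45 | 3 | 9 | 24 | 71% | 27 | 27 |
| 20 | 15 | 2 | 6 | 27 | 100% | 27 | 27 |
| 20 | 15 | 3 | 6 | 24 | 100% | 27 | 27 |
| 20 | 30 | 2 | 6 | 24 | 100% | 27 | 27 |
| 20 | 30 | 3 | 6 | 24 | 100% | 27 | 27 |
| 20 | 45 | 2 | 6 | 24 | 100% | 24 | 27 |
| 20 | 45 | 3 | 6 | 21 | 100% | 12 | 27 |

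At 20 × 10⁹/L the written rule falls short of the benchmark of 24 days by 3 to 18 days. At 50 × 10⁹/L the median is unchanged in 10 of 12 scenarios.

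**Step 3: a second model.** This one had 5,000 patients, a lognormal unsupported time to 20 × 10⁹/L (median 18 days, log-SD 0.25), 3-day sampling, and increments of 20 to 45 decaying over about 3 days. For ≥20 the median is 15 days as written and 21 days under the 7-day rule. For ≥50 it is 24 days under both. Against the assumed 18 days, the written rule is 18 − 15 = 3 days early and the 7-day rule is 21 − 18 = 3 days late, partly because of the sampling interval. The 6-day contrast is therefore not all error of the written rule.

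**Step 4: growth factors.** rhTPO and rhIL-11 raise the patient's own platelet production, so a count reached with them is not false recovery. The stated rhIL-11 range starts at 25 × 10⁹/L, so use within it cannot cause the crossing of 20, but the range does span 50. Their use bears on whether fast recovery can be credited to umbilical cord blood (UCB).

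**The case against.** The strongest reply is that the protocol gives thresholds without a dating rule, and that dating rules are commonly left to a statistical analysis plan, which is not shown here. This has force for the time origin, the choice of cycle and the handling of death or relapse before recovery. Those are unstated details, and they are not part of this point. It has less force for transfusion. The protocol states the qualifying condition itself, in its definitions section, and a transfused count meets that condition.

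Three other replies stand as limits:

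- Blood products are permitted, not mandated, and transfusion is one listed option among several. How often it was used is unknown.
- The endpoint is secondary and section 9.1 describes the analysis as mainly descriptive. No hypothesis or sample size rests on it.
- A transfusion-free window can overshoot, dating recovery late in a patient transfused shortly before true recovery. The second model shows this.

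A reader might infer that the trial's reported medians are in fact too short. The protocol does not support that: it contains no medians, and the analysis may have applied an unwritten transfusion rule. A reader might also infer that the growth factors inflate recovery in the same way as transfusions. They act through the patient's own production, so that mechanism does not apply.

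**Conclusion.** The point holds as a flaw in the definition. Applied literally, sections 2.2.2 and 6.2 let a transfusion-supported count qualify as platelet recovery. The direction is certain: equal or shorter, never longer. The 20 × 10⁹/L median can be biased short, while the 50 × 10⁹/L median is usually little affected.

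The size is not a trial figure. The modelled shortfalls at 20 × 10⁹/L depend on the assumed trigger, increment, platelet survival and recovery curve, and the true effect could be nil if few patients were transfused near the threshold. Only this secondary endpoint is touched; OS and EFS do not depend on it.

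**What to change.** In sections 2.2.2 and 6.2, define platelet recovery as the first of consecutive counts at or above the threshold with no platelet transfusion in a fixed, stated preceding window. Seven days would be one example. This is a measurement rule only and changes nothing about when patients are transfused. Re-derive the recovery dates from the transfusion records under that rule. If the analysis already used such a rule, it need only be written down. Report the use of rhTPO and rhIL-11 descriptively beside the medians.

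The cost is one sentence in each section and a check of transfusion records. Section 15 shows that enrolment and follow-up have ended, so the check is retrospective. Section 13 requires the source data to be kept, usually for five years after the end of the trial. The downside is that the medians, chiefly at 20 × 10⁹/L, may become longer, in part because any fixed window is somewhat conservative.
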